### The CAPEDP intervention

The intervention sought, where possible, to act upon the major modifiable determinants of infant mental health from the third trimester of pregnancy to the child’s second birthday. Intervention strategies were based upon three main theoretical concepts: parental empowerment, attachment security and Fraiberg’s developmental guidance and *Ghost in the Nursery* concepts [60]. With regard to parental empowerment, the programme manual used Rappaport’s [61] definition of empowerment as being made up of four components: participation, competence, self-esteem and personal and collective consciousness. The intervention thus specifically targeted mothers’ use of their personal community networks, their parenting skills, and their knowledge and use of available resources within the generous French social and health care context. Bowlby [62] defines attachment as a primary drive, a search for security through physical closeness when the child is in distress due to pain, hunger, stress, fear or separation. Depending on their mothers’ sensitivity and responsiveness to signals of distress, children develop, as early as 12 months of age, different styles of attachment. Secure attachment has been linked with increased resiliency, whereas insecure attachment and, even more so disorganized attachment, are associated with increased internalized and externalized psychopathology [63,64]. Increasing security of attachment and decreasing attachment disorganization were key intervention targets. Finally, providing social and emotional support within a solid working alliance to isolated, young mothers, often with difficult childhood experiences and high levels of postnatal depression, helped to connect the mothers’ past experiences with their behaviour when interacting with their child, thus uncovering potential ‘*Ghosts in the nursery’* and helping young mothers explore new ways of relating to their children.

As indicated above, a major specificity of the CAPEDP intervention was that the home-visiting intervention and its evaluation were entirely conducted by trained psychologists. Eleven psychologists were recruited and assigned to either the intervention team (n = 7) or the assessment team (n = 4). All home-visiting psychologists received intensive training on implementing the CAPEDP intervention. Using the theoretical bases described above, the intervention was tailored to target, in terms of maternal empowerment, mothers’ knowledge and skills with regard to parenting, their ability to make the most of the care system, and their involvement with their own personal and local community networks. In terms of mother-child relationships, increasing security of attachment and decreasing attachment disorganization were key intervention targets. Finally, home-visiting psychologists received training on providing social and emotional support to the mothers within a solidly constructed working alliance, and helping mothers connect their past experiences with their current behaviour when interacting with the child, identifying *ghosts in the nursery* and exploring new ways of relating to their children. Manualised, but tailored to each family’s needs, the intervention targeted objectives specific to each child development period: prenatal, 0 to 3 months, 3 to 6, 6–12, and 12 to 24 months. The manual drew from Weatherston’s work on home-visiting and reflective supervision [65], the Florida State *Partners for a Healthy Baby Home Visiting Curriculum *[66], and the *Steps Towards Effective Enjoyable Parenting* (STEEP) attachment-based program [67]. Extensive use was made of McDonough’s developmental guidance approach through the use of video clips, filmed and discussed with the mothers [68]. Visits included showing mothers films on different aspects of parenting, from delivery through the different stages of child development. Further details of the content of the intervention can be found elsewhere [69]. Training also included a specific section on ethics and research procedures.

The program was designed for psychologists to visit families six times during the antenatal period, eight times in the first three months of the child's life, 15 times when the child was between 4 and 12 months of age and another 15 times during the child's second year, resulting in a total of 44 home visits during the whole intervention. Between visits, phone calls could be made as often as necessary.

Each psychologist doing home visits had weekly individual supervision with a member of a team of psychiatrists and psychotherapists, as well as group supervision with the main investigator [name] to assess and react to situations of danger whether it be for the children (abuse, neglect, developmental delay, etc.) or their mothers (psychopathology requiring specific help, suicidal thoughts, special health needs etc.). Home visitors were encouraged to refer to the main investigator if they felt the slightest danger, if they felt distressed or if they felt that a situation was getting out of hand in any way.

### Description of the control group: usual care

Usual care, as described above, involved free access to the PMI network and to community mental health services, free antenatal maternity screenings by local GPs, extensive social security allowances and facilitated access to housing.

### Procedures and outcome measures

Families in the control group received usual care and seven assessment home visits across the trial period. The intervention group, in addition to usual care and assessment visits, received the CAPEDP home-visiting program. Assessment visits were conducted during specific home visits by a team of four trained and supervised psychologists, working independently from the psychologists performing the CAPEDP intervention, and with no prior knowledge of whether the families they were assessing were in the intervention group or the control group. For each family, seven home-based assessment visits were scheduled across the trial period, at the 27^th^ week of pregnancy, and then when the child was 3, 6, 12, 18 and 24 months old. All measured outcome criteria and the month at which these were measured are presented in Table 1. The assessment team received specific training on the use of all assessment instruments. Individual and group supervision was provided for all members of the assessment team, to give them support when faced with difficult situations during evaluation. Evaluators who observed significant problems or risk situations, either for the mother or for the child, in any family were instructed to seek immediate advice from the principal investigator. Families were referred to immediate care and support if necessary.

At baseline and, if appropriate, at follow up visits, the following data were collected: socio-demographic data including standard questions on age, sex, marital status, ethnicity, household composition, composition of the mother’s family, characteristics of the partner and, if different, the child’s father, whether the pregnancy was desired or not, number of years of education, educational level achieved, employment status, and income; health variables including mothers’ perceived state of health, and tobacco, alcohol or drug consumption. Neonatal data concerning the child and childbirth were collected while the mother was still in the maternity ward after giving birth.

As mentioned above, the study had three primary objectives: child mental health at the age of two as well as two potential mediating variables: maternal postnatal depression at three months postpartum and the quality of the home environment when the child was twelve months old.

Child mental health at the age of two was assessed using the Child Behavior Checklist 1½-5 (CBCL 1½-5) [70]. This instrument is widely used to assess psychopathology in infants and toddlers. A recent validation study in 23 societies, including the French translation and validation used in the present study, confirmed transcultural validity [45]. It is a 100-item scale, divided into seven syndrome subscales.

Maternal postnatal depression was assessed using the Edinburgh Postnatal Depression Scale (EPDS) [40]. This is a 10-item self-report questionnaire designed to be completed in the presence of an observer. It is valid for assessing both pre- and postpartum depression. The EPDS has been validated in a French population [71]. Different EPDS threshold scores were used to distinguish between depression and major depression.

The quality of the home environment when the child was 12 months old was assessed using the Home Observation for the Measurement of the Environment (HOME) [42]. This is a well-known and widely-used scale assessing the quality and quantity of stimulation and support available to a child in the home environment. As recommended, scoring was conducted during a home visit which did not have scoring the HOME as its unique objective.

Secondary outcome measures are described in Table 1.

The CAPEDP-A study assessed infant attachment quality, maternal disrupting behaviour and parental reflexive capacity using the Insightfulness Assessment (IA) interview.

Infant attachment quality was assessed using both the Strange Situation Procedure (SSP) [57] in our laboratory and the Attachment Q- Sort procedure [46], during a home visit. The SSP was used only in the CAPEDP-A subsample because of its complexity and time-consuming scoring. The procedure took place in an attachment assessment laboratory created specifically for this purpose in the research centre. The SSP proposes a fixed sequence of eight episodes, each lasting three minutes, designed to activate and/or to intensify the attachment behaviour of one year old infants. The procedure involves two brief separations and two reunions between the infant and their attachment figure, in the present case, their mother. Each procedure was video-taped. The procedure was coordinated by a senior psychiatrist trained in the use of the instrument and its coding. Psychology residents acted the roles of the strangers. The assessment of infant attachment quality using the SSP identifies three categories of attachment patterns. The insecure-avoidant group (A) is characterized by the infant avoiding manifesting attachment behaviour towards the attachment figure. The secure group (B) includes infants who evidence active proximity-seeking and interaction with the attachment figure, especially in reunion episodes. The insecure resistant/ambivalent group (C) is characterized by the coexistence of active contact resistance behaviour and proximity-seeking or contact-maintaining behaviour with the attachment figure. Coding of the procedure was made on video recordings by independent raters who were blinded to randomisation groups to reduce subjectivity-related variability. One assessment team and three coding teams were established. Coders had no direct contact with any dyad and were not aware of the group (intervention or control) to which the dyads belonged. Each measure was coded by separate coders. Furthermore, two independent coders coded a random selection of 30% of the cases. Inter-observer concordance calculated using Cohen’s Kappa coefficient was satisfactory (kappa = 0.79). Disagreements were discussed and a consensus category was attributed to the dyads in question. The SSP recordings were also used to assess disorganized attachment. Assessment was conducted by one of the authors [name], who was specifically trained and validated for this coding.

Maternal disrupting behaviour was assessed using the Atypical Maternal Behavior Instrument for Assessment and Classification (AMBIANCE) scale [58]. This 5-dimension scale, scored on the SSP procedure video, measures a broad range of maternal behaviors that can be potentially disorganizing to infants' attachment. Higher scores reflect higher levels of maternal disorganising behaviour when attachment issues are raised. The scoring team was trained by [name] and [name], the creators of the AMBIANCE scale, in a training session in Paris in 2008 and demonstrated full reliability. AMBIANCE coders were different from SSP coders and blind to the randomisation group of the families being assessed.

Parental reflexive capacity was assessed using the Insightfulness Assessment (IA) interview [59]. This is a semi-structured interview concerning the mother’s capacity to see things from the child’s point of view. It is assessed after she has viewed a video clip of herself with her child (nappy changes, free play, feeding or SSP). The IA is scored using ten sub-scales, and results in a classification into four categories. Each dyad was video-taped for SSP, nappy change, feeding and free play. The four IA raters achieved reliability on IA rating during a specific 2007 training with the team that created the instrument. Raters for IA were blind to the randomisation group of the dyad. The IA interviews took place at the same time as the SSP, when the infant was from 12 to 15 months of age.

Psychologists were asked to keep case notes on each home visit. These will be used to evaluate the frequency of the different themes that were notified as discussed during the home visit, the home visitor’s subjective perception of the visit, and the extent to which the home visitors’ preoccupations during that visit corresponded to the intended intervention.

### Adherence and withdrawal

Participants were informed that they could withdraw at any time for any reason. In order to optimise adherence to the intervention, families were reminded of upcoming visits by phone or with a text message. Missed home visits were rescheduled within the following week. Home visitors were also encouraged to maintain telephone contact with families between visits. Families that regularly missed home visits or did not respond to phone calls continued to receive regular calls at least once a fortnight from their home visitor. These calls continued through to the end of their planned participation in the study. Letters were regularly sent to each family that had not been in direct contact with their home visitor for a period of over three months without giving news. All participants, including those lost to follow up by the intervention team, were contacted by the evaluation team at every assessment point (at 3, 6, 12, 18, 24 months). In cases where families accepted phone contact but were reticent to receiving any further home visits, assessment took place over the telephone, except for those instruments that required direct observation. If phone contact proved to be impossible, questionnaires were sent to families via the post.

### Statistical analysis

#### Determination of sample size

The trial was designed to establish whether the CAPEDP intervention was superior to usual care in terms of postnatal maternal depression prevention as assessed using the EPDS, the quality of the home environment assessed with the HOME, and child psychopathology, assessed using the CBCL 1½-5.

Regarding the prevention of postnatal maternal depression, assuming a mean of 12.1 on the EPDS (SD 4.6) for the usual care group [41], 113 participants per study group would be sufficient to detect a 2-point decrease in the EPDS with 90% power at a 2*-*sided significance level of α = 5%.

Regarding quality of the home environment, assuming a mean of 25.5 on the HOME (SD 4.3) for the usual care group [72], 99 participants in each study group would provide 90% power at a two-sided α = 5% to detect a 2-point increase in the HOME.

Regarding infant psychopathology, assuming a mean score of 48.5 on the CBCL 1½-5 (SD 8.95) for the usual care group [73], 189 participants in each study group would provide 90% power at a two-sided α = 5% to detect a 3-point difference in the CBCL 1½-5.

To account for possible patients lost to follow up and have sufficient power to answer all three primary objectives, the project planned to recruit 440 families.

#### Statistical analysis

The data will be summarized using mean, median, standard deviation and range for continuous data and counts or percentages for categorical data.

##### Primary analyses

The data will be analyzed according to the modified intention-to-treat principle: all participants are taken into account within their particular assignment group whatever might have happened during the study, and all randomized participants that have at least one assessment visit within the first year of follow-up will be included for analysis. Missing data will be handled using multiple imputation and sensitivity analyses will be conducted. The between-group absolute differences in the EPDS score when the child is 3 months old, the HOME score at 12 months and the CBCL score at 24 months will be analyzed using Student’s t tests.

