### Study population

Eligibility criteria limited participation to mothers in situations of medium to high vulnerability with regard to their future child’s mental health. All consecutive women consulting in the second trimester of pregnancy (from 12 to 27 weeks of amenorrhea) in ten public maternity wards were assessed for eligibility. Pregnant women were eligible if they were: living in the intervention area (Paris and its inner suburbs); sufficiently fluent in French to give valid informed consent, benefit from the intervention and participate in assessment sessions; less than 26 years old; first time mothers; less than 27 weeks pregnant at their first home visit assessment session; eligible for legal national health insurance or its equivalent for non-French participants (as required by French law on clinical research). They also had to declare at least one of the three following criteria: 1) having less than twelve years of education, 2) intending to bring up their child without the presence of the child’s father, and 3) having low income, defined as being eligible for French social welfare health insurance (*Couverture Maladie Universelle Complémentaire*) i.e. with an income less than or equal to 850 euros a month or, for undocumented migrants, Government Medical Aid (*Aide médicale d’Etat*).

Exclusion criteria were: women who would be impossible to follow up, such as Roma, gypsies, travelers, the homeless, or temporary refugees; women already receiving sustained social or medical care for other reasons than the above inclusion criteria (such as addictions or mental or physical disorders requiring close long-term follow-up); and women who did not consent to participate.

Participation in the study was proposed to eligible women in the waiting rooms of each maternity hospital, prior to a prenatal appointment. During this interview or at a second appointment if she asked for more time to make up her mind, the future participant signed the informed consent form.

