Another limitation is that randomisation was performed at inclusion, rather than after the first assessment visit. A significant number of randomized women withdrew their consent to participate before any data had been collected. This will necessarily result in a modified intent to treat analysis, a classical intent to treat analysis being impossible.

Furthermore, it must be underlined that women who were not fluent enough in French to give informed consent to participate or who were already receiving other types of clinical interventions were not eligible for inclusion in the present study. Similarly families for whom home-visiting would be impossible, for example Roma, gypsy or traveller families, transient refugees or homeless women were excluded. Generalising from results from this study to all mother-child dyads in multi-risk social situations will therefore be hazardous.

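### The primary analysis set requires an assessment visit in the first year, a cut-off the protocol does not justify and which can discard an observed 24-month CBCL

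*Protocol article*

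**What the plan says.** The Primary analyses section of the protocol article describes a modified intention-to-treat analysis. It first says that "all participants are taken into account within their particular assignment group whatever might have happened during the study", then sets the condition for membership: "all randomized participants that have at least one assessment visit within the first year of follow-up will be included for analysis". The same rule serves the EPDS at 3 months, the HOME at 12 months and the CBCL at 24 months. It adds: "Missing data will be handled using multiple imputation and sensitivity analyses will be conducted".

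Three other places bear on the rule:

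- **Randomisation and masking.** Women were randomised after screening and consent. From then on they knew their arm; only the outcome assessors were blinded.
- **Adherence and withdrawal.** "All participants, including those lost to follow up by the intervention team, were contacted by the evaluation team at every assessment point", and the list of points runs to 24 months. Families who refused further visits could be assessed by telephone, apart from instruments needing direct observation. Failing that, "questionnaires were sent to families via the post".
- **Discussion, limitations.** Randomisation came before the first assessment visit. The reason given for a modified set is that "A significant number of randomized women withdrew their consent to participate before any data had been collected".

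**The concern.** Because randomisation preceded every assessment visit, attending one is something a woman does after learning her arm. The documents describe pressures that could act differently in the two arms. The intervention arm was offered 44 psychologist visits, which the Discussion says some mothers may find stigmatising. That arm also had reminders, regular calls and letters from a home visitor, whom the control arm did not have. Selection could therefore go in either direction, and blinded assessors do not prevent it.

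The first-year limit makes this worse than it need be. It closes entry to the set about a year before the CBCL is measured, in a trial that kept contacting everyone. A woman first reached at 18 or 24 months is removed even if she supplies the primary outcome. As written, multiple imputation operates inside the selected set, so it cannot bring her back.

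**Working it through.** **1. The stated reason against the stated rule.** The Discussion's reason covers women who withdrew consent before any data were collected. The rule excludes a wider group: everyone without a first-year assessment visit. The difference between the two groups is the women who did not withdraw, had no first-year visit, and were reached at 18 or 24 months. Nothing in the article gives a reason for excluding them.

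**2. Can such women exist?** Assessments were scheduled at the 27th week of pregnancy and at 3, 6, 12, 18 and 24 months. If the prenatal visit counts, a woman must miss four in a row (week 27, then 3, 6 and 12 months) and then be reached. Contact at every point makes that possible by design, but it is probably uncommon.

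**3. Unsettled wording.** The article does not say when the first year starts. From birth, the 12-month visit lies at the edge of the window. From the 27th week of pregnancy, assuming birth at 40 weeks, it falls at about 3 + 12 = 15 months, outside it. Nor does it say whether a telephone or postal assessment counts as a visit. Under each reading the rule can still remove an observed 24-month CBCL.

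**4. The plan's own figures.** Inputs from Determination of sample size: CBCL SD 8.95, target 3 points, 90% power, two-sided 5%. The exact two-sample t-test gives 189 per arm, as stated. Planned recruitment is 440/2 = 220 per arm, which allows a loss of 1 − 189/220 = 14.1%. The sample size is sound; the issue is bias.

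**5. Size of the avoidable bias.** Let p_I and p_C be the shares of late returners in the intervention and control arms, and D the mean CBCL gap between them and the retained women, taken as equal in both arms. The full mean in an arm is the retained mean + p × D, so leaving late returners out shifts the between-arm difference by (p_I − p_C) × D in size. The documents give neither quantity. Assumed ranges: 2 to 5 percentage points (about 4 to 11 women out of 220) and 0.5 to 1 SD.

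- 0.02 × 0.5 × 8.95 = 0.09 points; 0.09/3 = 3% of target
- 0.02 × 1.0 × 8.95 = 0.18 points; 6%
- 0.05 × 0.5 × 8.95 = 0.22 points; 7%
- 0.05 × 1.0 × 8.95 = 0.45 points; 15%

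With p_I = p_C and the same D in both arms, the bias is zero.

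**6. Effect on the test.** At 189 per arm the standard error of the difference is 8.95 × √(2/189) = 0.92. With no true effect, a bias of 0.45 raises the two-sided 5% error rate to about 7.8% (normal approximation); a bias of 0.09 leaves it at about 5.1%.

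**The case against.** The strongest reply is that the main selection is already disclosed. The article calls the set modified, lists it as a limitation, explains that women withdrew before any data existed, and plans imputation and sensitivity analyses. Exclusion counts by arm and the content of those analyses normally belong in a statistical analysis plan, which is not shown, so their absence is no fault here. This stands for women with no data. It does not reach the first-year limit, which the article fixes and does not explain.

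A second reply is that few women can miss four consecutive assessments and then return. That may be so. It limits the size of the problem but gives no reason to discard those who do.

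A reader might also infer several stronger points that the text does not support:

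- **That the rule contradicts itself.** The first clause can be read as governing the arm in which a woman is analysed, and the second as governing who enters the set. That is a common modified intention-to-treat construction, loosely worded.
- **That women followed only by telephone or post are excluded.** This is one reading. The article treats telephone contact as a way of carrying out an assessment and does not say that it fails to count.
- **That women are dropped for a late first visit.** Study population requires women to be "less than 27 weeks pregnant at their first home visit assessment session", but that is an eligibility criterion; the analysis section states no exclusion on that ground.
- **That withdrawals per arm are known.** The trial team may hold them through central randomisation, but the article gives no count and no split.

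**Conclusion.** The concern holds for the first-year condition. It selects on behaviour after open-label randomisation, can discard an observed primary CBCL, and has no stated justification. Loss of women who withdrew before data collection is disclosed and partly unavoidable, and is not the fault identified here.

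The number of women affected cannot be derived from the article and may be small. On the assumed inputs the avoidable bias is about 0.09 to 0.45 CBCL points, 3% to 15% of the target difference, and zero when share and gap match across arms. A reader might apply the same formula to all excluded women; a 20-point difference in exclusion and a gap of 1 SD would give 0.20 × 1.0 × 8.95 = 1.79 points, 60% of the target. That figure does not describe the first-year cut-off, because most of those women would have no outcome data. Removing the condition would not recover them, and imputing them from centre and eligibility items would help only as far as those items predict the CBCL.

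**What to change.** Remove the first-year condition. Define the primary set as every randomised woman, analysed as assigned, with any usable assessment at any time up to 24 months, whether by visit, telephone or post. Run the multiple imputation over that set. This also settles the start of the first year and the meaning of an assessment visit, since neither then matters.

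Report the number excluded in each arm with the reason. For women who withdrew before data collection, add a delta (tipping-point) sensitivity analysis. It needs only their counts by arm: each arm's mean is shifted by its withdrawn share times an assumed gap, and the gap is varied until the conclusion changes. This explores the unavoidable part of the selection; it does not remove it.

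The cost is a change of wording, a little more imputation work and possibly slightly wider intervals, since late returners will need imputed EPDS and HOME scores.
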